### Evaluation of results (definitions and response/evaluation of outcome measures)

The primary assessment of efficacy is carried out at the completion of the trial (once all patients for cohort 7 have completed the 12 months follow-up or the last patient last visit) for the 2.5 mg/kg dose of ATG and using the primary outcome of area under the stimulated C-peptide response curve over the first 2 hours of the MMTT at 12 months follow-up. We will transform the MMTT AUC C-peptide value to ln(AUC C-peptide +1). The primary analysis will be a statistical significance test.

### Statistical methods for primary analyses

The primary endpoint, the area under the C-peptide curve over the first 2 hours (using all available measurements within the first 2 hours) of an MMTT (AUC C-peptide) at 12 months (after transformation) will be analysed using a linear regression model at the end of the trial. The model will have fixed effects of time and categorical dose along with an interaction term between time and dose with participant as a random effect and the baseline measurement of MMTT AUC C-peptide (transformed using the ln(x+1) function). The primary contrast of interest is the mean difference in transformed MMTT AUC C-peptide between dose level 2.5 mg/kg and placebo with a 95% CI. The statistical test will be the Wald test or t-test on the 2.5 mg/kg parameter in the model and significance is assessed at the 5% level. If there is a significant effect for the 2.5 mg/kg versus placebo mean difference, then every other dose level will be compared with the placebo dose at the 5% level using t-tests. If there is not a significant effect for the 2.5 mg/kg dose, then no other tests will be carried out. This forms a closed testing procedure for the primary endpoint and the family wise error rate is controlled at 5%. The lowest dose below 2.5 mg/kg that is found to be statistically significantly different to placebo will be declared the minimally effective low dose (MELD).

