## Introduction

### Background

Type 1 diabetes (T1D) is a chronic autoimmune disease, characterised by progressive destruction and dysfunction of the insulin-producing β cells of the pancreas. The incidence of T1D is increasing and around 130 000 children and adolescents worldwide will develop T1D each year.^1–3^ A diagnosis of T1D is associated with a lifelong dependence on insulin therapy. The primary goal of therapy is to maintain glycaemic control as assessed by glycated haemoglobin (HbA1c), in a range sufficient to prevent long-term renal, cardiac and retinal complications as shown in the Diabetes Control and Complications Trial.^4^ However, recent data arising from continuous glucose monitoring (CGM) suggests that as well as avoidance of hypoglycaemia, improved ‘time in target’ may also be an important patient-related outcome.^5 6^ Technological advances and the increasing uses of insulin pumps and glucose sensors are gradually having an impact on glycaemic trends, but few people achieve glycaemic targets of <7%–7.5% (<53–58 mmol/mol) recommended by recent guidelines to prevent long term complications.^7^

Development of T1D is triggered by pancreatic islet-specific CD4 + and CD8+T cells, as well as B cells, which target and eliminate insulin-producing β cells. Recent epidemiological data indicate that the pathogenic mechanisms which lead to destruction of β cells may already begin soon after birth and by the time of diagnosis (peak between 5 and 15 years) residual functional β cell mass may be reduced already by around 50%.^8 9^ Although still a subject of investigation, there is no evidence that even intensive insulin therapy starting right after T1D diagnosis will be able to prevent further deterioration in β cell function. Paediatric patients will lose up to 50% of residual β cell function over the first year from diagnosis, while adults lose about 15%.^10^ Thereafter, decline in β cell function is highly variable and evidence of persisting active β cell function may be observed many years later particularly in those diagnosed during adult life.^11–13^ Preservation of some β cell function, as assessed by a Mixed Meal Tolerance Test (MMTT), is associated with improved glycaemic control, reduction in hypoglycaemia risk and significant reductions in the risk for progression of retinopathy and other long-term complications.^14 15^

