**Figure 1 F1:**
[figure not shown]
MELD-ATG design. ATG total dose (mg/kg) will be divided into ttwo infusions on wo consective days. For safety, recruitment in cohort 1 will start in 12–25 years old before stepping down to <12 years old. *Middle dose(s) will be adjusted individually by cohort by the DDC and IDMC for cohorts 2–7 following review of all toxicity and early efficacy data of the preceding cohort(s). Middle dose(s) selected for the next cohort may differ from those selected for previous cohorts. ATG, antithymocyte globulin; DDC, Dose Determining Committee; IDMC, independent data monitoring committee; MELD, minimal effective low dose.

Participants newly diagnosed with T1D within 3–9 weeks of planned treatment day 1 will be recruited sequentially into seven different cohorts. MELD-ATG is an international multicentre trial. The trial will include suitable sites across Europe who are part of the existing INNODIA T1D clinical consortium (www.innodia.eu) and that are confirmed suitable for undertaking this specific trial through an accreditation process. Currently, 12 clinical sites across 10 European countries are planned to be incorporated, and include Belgium, the UK, Austria, Denmark, Finland, Germany, Poland, Slovenia and Italy. Further details on participating sites can be obtained from the MELD-ATG Coordinating team contact ([contact]) and via the INNODIA web page (Innodia.eu - Clinical Trials).

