### Trial participants, study design and oversight

There will be continuous recruitment of 114 participants, divided into seven sequential cohorts with variable dose allocation.

The first cohort of 30 participants will be randomised to 5 intervention arms, namely placebo, 2.5 mg/kg, 1.5 mg/kg, 0.5 mg/kg and 0.1 mg/kg ATG total dose in a 1:1:1:1:1 allocation ratio stratified by two age groups 12–17 and 18–25. Recruitment will initially be limited to 12–25 year olds until the first 10 participants 12–17 years of age to receive a non-placebo dose of ATG have been observed for 4 weeks after last dose administration. For the age step-down, a dose determining committee (DDC) will examine the safety data in this initial group of 10 non-placebo dose participants 12–17 years of age and will determine whether it is safe to recruit younger participants (aged 5–11 years) into the trial. The independent data monitoring committee (IDMC) will review the DDC decision for the safety age step down analysis and will need to give final approval to allow the step down in age to occur.

The rationale for this step down is that ATG has not yet been used in this indication and at these doses in paediatric participants aged 5–11 years. New-onset T1D participants aged 12–45 were already treated with 2.5 mg/kg ATG in a previous clinical trial by Haller *et al* reported in 2018 and 2019 and and no concerning safety signals were seen in the 1 year trial with 5-year follow up.^25 26 29^

Once the age step-down has occurred, randomisation into cohort 1 will continue until 30 participants have been randomised, in a 1:1:1:1:1 allocation ratio within three age stratification groups (5–9, 10–17 and 18–25). After cohort 1 has been recruited, recruitment to cohort 2 will begin, including stratification to the three age groups (5–9, 10–17 and 18–25).

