Cohort 2 will consist of 12 participants randomised to 4 intervention arms, placebo, ATG 2.5 mg/kg and two middle ATG doses, in a 1:1:1:1 allocation ratio stratified by the three age groups. The choice of the middle doses will be made by the DDC using all available clinical, mechanistic and safety data from the previous cohort’s data. Further a Bayesian model’s predictions, using all MMTT C-peptide measurements in cohort 1 up to 12 months follow-up, will be used to help recommend cohort 2’s middle dose selections to the DDC. CD4 + and CD8+T cell counts will also be used for the DDC’s decision because as shown by Haller *et al*^26^ they represent an effectivity indicator for dose action: If these levels do not change then that dose will not be allowed to be taken forward regardless of the recommendation of the Bayesian model. The DDC will be required to come to a complete consensus for the middle dose(s) allocated to the next cohort. After cohort 2 has been recruited, recruitment to cohort 3 will begin.

Cohort 3 will consist of 12 participants randomised to 4 intervention arms, placebo, 2.5 mg/kg ATG and two middle doses decided by the DDC, in a 1:1:1:1 allocation ratio stratified by the three age groups. The DDC will be convened to determine the two middle doses to be applied to cohort 3 following the same procedure as described above, using all MMTT C-peptide measurements for all participants in all previous cohorts up to 12 months follow-up. The middle doses selected for cohort 3, or indeed any future cohorts, may be different to those selected for cohort 2, or previous cohorts. After cohort 3 has been recruited, recruitment to cohort 4 will begin.

Cohort 4 will consist of 15 participants randomised to 3 intervention arms, placebo, 2.5 mg/kg ATG and a single selected middle dose decided by the DDC, in a 1:1:1 allocation ratio stratified by the three age groups. The DDC will again be convened to determine the one middle dose to be used in cohort 4, following the same procedure as described above.

Cohorts 5, 6 and 7 will each consist of 15 participants randomised to three intervention arms, placebo, 2.5 mg/kg and selected middle doses, in a 1:1:1 allocation ratio within each age group. The above-described process will continue for each cohort up to Cohort 7 with additional individual interim analyses to identify the middle doses to be used in cohorts 5–7.

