### Randomisation and blinding

Following written informed consent/assent, participants will be allocated a unique participant trial ID number and only deidentifiable information (partial date of birth and sex) will be collected. Participants will be randomised centrally using a web-based randomisation system (Sealed Envelope at https://www.sealedenvelope.com/).

Randomisation will be based on block randomisation within age strata: 5–9, 10–17 and 18–25 years. Five blocks will be used for cohort 1, to be generated by Sealed Envelope. Subsequently the modified randomisation lists provided by Cambridge Clinical Trials Unit (CCTU) will use four blocks for cohorts 2–3, and three blocks for cohorts 4–7. The allocation ratios are: 1:1:1:1:1 for cohort 1, 1:1:1:1 for cohorts 2 and 3 and 1:1:1 for cohorts 4–7 within each age strata. Treatment will be randomly assigned in each cohort sequentially as described above. Access to the web-based randomisation system will provided to designated individuals at participating sites, via individual user accounts, and instructions will be provided in the MELD-ATG Trial Manual.

Trial participants and research teams will be blinded to the treatment allocation for the duration of the trial. Site pharmacies are unblinded. Randomisation is blinded. A concealment list is provided to the pharmacist in order to unblind and prepare the appropriate infusion. The unblinded individuals keep the treatment information confidential and will not discuss or release information on treatment allocation. Pharmacies prepare the infusions of ATG and placebo so that they are similar in packaging and labelling.

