### Statistical methods for secondary analyses

The secondary endpoints measured repeatedly over time will be analysed via a mixed effects model. Within the model time and categorical dose will be fixed effects along with an interaction term between time and dose with participant as a random effect. If required, the models may include additional covariates which may be potential factors that are confounding the relationship between dose and outcomes. The main additional covariate will be age of diagnosis. Subgroup analyses will be considered for a select list of potential covariates, the subgroup treatment effect will be analysed using an interaction test and additional factors will be included in the model to conduct this test. As an extra sensitivity analysis, we will assume a linear effect of dose and rerun the model with that assumption. A detailed statistical analysis plan will be produced before the final database lock.

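### The primary model omits the age strata used to randomise, and middle doses dropped early are tested against placebo pooled over all seven cohorts, which leaves those tests open to confounding

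*Protocol article*

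**What the plan says.** - **Primary model** (Statistical methods for primary analyses): time, categorical dose and time-by-dose as fixed effects, "with participant as a random effect and the baseline measurement of MMTT AUC C-peptide (transformed using the ln(x+1) function"). If 2.5 mg/kg is significant, every other dose is then tested against placebo, with no restriction to placebo participants of the same cohorts.
- **Other models**: the model under Procedure to account for missing or spurious data and the Bayesian model under Interim analyses also have no age or cohort term.
- **Randomisation** (Randomisation and blinding): "Randomisation will be based on block randomisation within age strata: 5–9, 10–17 and 18–25 years". Lists run separately for each cohort.
- **Age mix** (Trial participants, study design and oversight): "Recruitment will initially be limited to 12–25 year olds until the first 10 participants 12–17 years of age" on active drug have been observed for 4 weeks. Ages 5–11 enter after that.
- **Middle doses** (Figure 1 legend): "Middle dose(s) selected for the next cohort may differ from those selected for previous cohorts". The design section repeats this for cohort 3 onwards.
- **Age as a prognostic factor** (Background): "Paediatric patients will lose up to 50% of residual β cell function over the first year from diagnosis, while adults lose about 15" per cent.
- **Age as a covariate** appears only under Statistical methods for secondary analyses, to be used if required: "The main additional covariate will be age of diagnosis". Cohort appears in no model.

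**The concern.** The protocol stratifies by age, describes age as a strong driver of the outcome, and then leaves it out of the model that decides the trial. The model's terms are listed one by one, so this is a stated choice and not a detail left for the SAP.

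The second issue is separate. Randomisation protects a comparison only within a cohort. Placebo is planned in every cohort (6+3+3+5+5+5+5 = 32), but a middle dose may appear in only some of them. For a dose used in cohort 1 alone, 26 of the 32 placebo participants are not concurrent. If cohorts differ in age mix or over calendar time, that difference enters the dose effect. Baseline C-peptide adjusts for the starting level, not for a difference in the rate of loss. The minimally effective dose is the lowest significant one, so a single biased low-dose test could decide it.

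**Working it through.** **1. The plan's own figures.** Inputs from the sample size section: SD 0.27, difference 0.22 on ln(AUC+1), two-sided 5%, 90% power.

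n = 2 × (1.960 + 1.282)² × (0.27/0.22)² = 31.7, so 32 per arm, as stated. The noncentral t gives 89.4% power at 32 per arm. For a middle dose with 30 against 32 and a difference of 0.20 it gives 81.8%, consistent with the stated 80%.

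**2. Size of the age gap.** Apply the Background losses (50% and 15%) to the mean AUC of 0.77:

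ln(1 + 0.77 × 0.85) − ln(1 + 0.77 × 0.50) = ln(1.6545) − ln(1.385) = 0.178.

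This is an upper-end value, because the paediatric figure is a maximum and the adult figure is not. Half of it, 0.089, serves as a lower value. The documents give no gap on the transformed scale.

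**3. Precision lost by omitting age.** With adult share p (assumed 15–35%) and gap g, R² = p(1 − p)g²/0.27².

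- Low end: 0.15 × 0.85 × 0.089²/0.0729 = 1.4%, SD 0.268. Power is 89.8% for 2.5 mg/kg and 82.3% for a 30-person middle dose.
- High end: 0.35 × 0.65 × 0.178²/0.0729 = 9.9%, SD 0.256. Power is 92.2% and 85.6%.

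The gain is about 0.4 to 3 points for 2.5 mg/kg and 0.5 to 4 for a middle dose. It is smaller if baseline C-peptide already carries part of the age effect.

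**4. Bias from age mix in a middle-dose test.** Let p1 be the adult share in cohort 1, p2 the share later, and f the fraction of the dose's participants who come from cohort 1. For placebo that fraction is 6/32. Then

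bias = g × (p1 − p2) × (f − 6/32).

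The documents give no adult shares; these are assumptions. With g = 0.178 (type I error from 40,000 simulated null trials, two-sample t-test, nominal 5%):

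| Dose used in | n | f − 6/32 | Bias, adults 40% then 25% | Bias, adults 60% then 15% | Type I error |
|---|---|---|---|---|---|
| All seven cohorts | 32 | 0 | 0 | 0 | about 5% |
| Cohorts 1 and 4–7 | 26 | 0.043 | 0.001 | 0.0035 | about 5% |
| Cohorts 1–3 | 12 | 0.3125 | 0.008 | 0.025 | 5.1–5.7% |
| Cohort 1 only | 6 | 0.8125 | 0.022 | 0.065 | 5.3–8.7% |

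With g = 0.089 the biases halve. The largest, 0.065, is about a third of the 0.20 middle-dose target.

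**5. Bias from calendar time.** Assume a shift s in outcome from cohort 4 onwards. Of the 32 placebo participants, 20 come from those cohorts. A dose stopped by cohort 3 is biased by −s × 20/32, which is −0.031 for s = 0.05 and −0.063 for s = 0.10.

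**6. What a cohort term does to the standard error.** Least squares on the planned cohort sizes, SD 0.27, no true cohort effect:

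- 2.5 mg/kg, or a middle dose in all cohorts: 0.0675 with or without the term.
- Cohorts 1 and 4–7: 0.0713 to 0.0725.
- Cohorts 1–3: 0.091 to 0.098–0.099.
- Cohort 1 only: 0.27 × √(1/6 + 1/32) = 0.120 without the term, 0.131 with it.

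**7. The 2.5 mg/kg contrast.** As planned, both arms have 6, 3, 3, 5, 5, 5 and 5 participants by cohort, so any difference between cohorts cancels.

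**The case against.** A reader might infer that all middle-dose comparisons are confounded and that every test loses precision. The documents support neither:

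- Bias depends on the path of the dose. It is zero for a dose used in every cohort and below 0.004 for cohorts 1 and 4–7. The large values belong to a dose given to 6 participants and then dropped. Its test has about 38% power for a true 0.20 and runs only if 2.5 mg/kg succeeds.
- Precision is lost only by omitting age. A cohort term leaves the 2.5 mg/kg standard error unchanged and widens it for partly carried doses. The reason to consider cohort is bias.
- The planned primary contrast is not biased.

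The size is also uncertain. The step-down rule excludes ages 5–11 at first, not children in general. It needs 10 actively treated participants aged 12–17, about 12.5 in all at 4:1 active to placebo, so adults can be at most about 17.5/30 = 58% of cohort 1. The 60% scenario is therefore a ceiling. The Background contrasts children with adults and gives no difference between 5–11 and 12–17, the groups that the step-down separates.

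Finally, the protocol does allow an age covariate where needed in the secondary analyses, and C-peptide at 12 months is among those endpoints. That is optional, however, and does not govern the test that names the minimally effective dose.

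These points limit the reach of the concern. They do not remove the missing strata or the pooled non-concurrent placebo.

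**Conclusion.** The concern holds in two limited parts.

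1. The primary model omits the age strata used to randomise, although the protocol makes age prognostic. The cost is modest: about 0.4 to 3 power points for 2.5 mg/kg, assuming 15–35% adults and a gap of 0.089–0.178.
2. A middle dose dropped early is open to confounding by age mix and calendar time, because its placebo group is pooled over all seven cohorts. With the upper-end gap and assumed age shares, the age-mix bias is roughly 0.02–0.065 for cohort 1 only, 0.01–0.025 for cohorts 1–3, and near zero for a dose carried through most cohorts. A calendar shift could push the other way.

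The 2.5 mg/kg versus placebo contrast is exposed only if the allocation ratio changes between cohorts. The protocol allows that: the dose committee may use placebo or 2.5 mg/kg as the middle dose to restore numbers, and the interim rule sends the next cohort to 2.5 mg/kg if no other dose qualifies.

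**What to change.** - Add age stratum (5–9, 10–17, 18–25) and its interaction with time to the primary model, including the middle-dose comparisons. The interaction is needed because the issue is a difference in rate of loss. With linear loss and equal weight at 3, 6 and 12 months, the gaps from step 2 are 0.040, 0.082 and 0.178. Their mean, 0.100, is only about 56% of the 12-month gap, so a main effect alone would leave much of it.
- For middle-dose tests, prespecify a cohort-adjusted or concurrent-placebo analysis, at least as a sensitivity analysis.
- Align the model descriptions under Statistical methods for secondary analyses, Interim analyses, and Procedure to account for missing or spurious data.

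Cost: wording, and a few degrees of freedom (2 for age, 4 for its interaction with three categorical follow-up visits, 6 for cohort where used). The 2.5 mg/kg standard error does not change with cohort in the model. Intervals widen somewhat for doses used in few cohorts, for example a standard error of 0.120 to 0.131 for cohort 1 only.

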1. To determine the effects of ATG treatment on stimulated C-peptide	1. The area under the stimulated C-peptide response curve over the first 2 hours of an MMTT measured throughout the study in different ATG dosage groups	1. Baseline, 3, 6, 12 months
2. To determine the effects of ATG treatment on HbA1c	2. HbA1c measurements measured throughout the study in different ATG dosage groups in mmol/mol	2. Baseline, 3, 6, 12 months
3. To determine the effects of ATG treatment on intermittent CGM measures	3. CGM measures (time in range, time above, time below) measured throughout the study in all different ATG dosage groups and placebo	3. For 14 days at 3, 6, 12 months
4. To determine the effects of ATG treatment on fasting and stimulated DBS C-peptide measurements	4. DBS C-peptide measurements measured throughout the study in all different ATG dosage groups and placebo in pmol/L at 0 min and 60 min	4. Baseline, monthly
5. To determine whether ATG treatment mediates a reduction in CD4-positive T cells but relative preservation of CD8-positive T cells	5. CD4-positive T cells and CD8-positive T cells measured throughout the study in different dosage groups	5. Baseline, 1, 2, 4 weeks and 3, 6, 12 months
6. Descriptive analysis of the safety profile of different doses of ATG in different age groups	6. Safety will be assessed at each visit by physical examination, including assessment of the most commonly reported reactions to ATG, namely serum sickness, CD4 + lymphocyte decrease, cytokine release syndrome, fever, influenza-like symptoms and rash; vital signs (temperature, blood pressure, heart rate); weight, abnormal laboratory parameters (liver, kidney function, full blood count); reporting of adverse events in different dosage groups	6. Baseline, treatment day 1 and 2, 1, 2, 4 weeks and 3, 6, 12 months
7. To determine the effects of ATG treatment on T1D-associated autoantibodies (GADA, IAA, IA-2A and ZnT8A)	7. T1D-associated autoantibodies (GADA, IAA, IA-2A and ZnT8A) at the start and end of the study	7. Screening, 12 months
8. To determine the effects of ATG treatment on insulin requirements	8. Insulin requirements measured throughout the study in all different ATG dosage groups	8. Baseline, 1, 2, 4 weeks and 3, 6, 12 months
Exploratory objectives		

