### Procedure to account for missing or spurious data

For all key endpoints including the area under the stimulated C-peptide response curve over the first 2 hours of an MMTT at 12 months post-treatment, CD4 +T cells and CD8 +T cells and fasting/stimulated DBS C-peptide measurements a repeated measures mixed effects model will be used as the analysis allowing outcomes with missing data to be incorporated. All participants who are randomised will be included in this analysis and the model will have fixed effects for time and dose along with an interaction term between time and dose and participant is a random effect. All available repeated measurements of MMTT AUC C-peptide in the same individual over time will be included in the analysis and an unstructured autocorrelation will be estimated for each dose level if the data allow. These estimates assume that the missing data are missing at random. If the missing data is non-ignorable then a sensitivity analysis will be performed. The secondary endpoints will also be analysed using a mixed effects model similar to the one described above.

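### The primary model gives baseline C-peptide one slope for all visits; if that slope weakens by 12 months, a baseline-by-visit term would recover a modest amount of precision at almost no cost

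*Protocol article*

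**What the plan says.** The protocol article, under statistical methods for primary analyses, says that the transformed 12-month AUC "will be analysed using a linear regression model at the end of the trial". It then names visit time and dose (as a category) as fixed effects, allows the two to interact, and finishes its list of terms thus: "with participant as a random effect and the baseline measurement of MMTT AUC C-peptide (transformed using the ln(x+1) function". No interaction between baseline and time appears there or anywhere else in the article.

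The section on missing or spurious data makes clear that the analysis uses repeated visits: "All available repeated measurements of MMTT AUC C-peptide in the same individual over time will be included in the analysis". Table 1, under Objectives, gives the visits as "Baseline, 3, 6, 12 months", so three follow the baseline. The same missing-data section restates the fixed part as "the model will have fixed effects for time and dose along with an interaction term between time and dose and participant is a random effect", this time without a baseline covariate, and adds that "an unstructured autocorrelation will be estimated for each dose level if the data allow".

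The Background describes an uneven course after diagnosis: "Paediatric patients will lose up to 50% of residual β cell function over the first year from diagnosis, while adults lose about 15" per cent.

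**The concern.** A model with time, time-by-dose and a participant random effect needs several visits per person. In such a model a baseline main effect has the same coefficient at every visit. The primary endpoint concerns only the 12-month visit, so the slope that serves it best is the 12-month slope.

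Participants are 5 to 25 years old and, on the protocol's own account, lose function at very different rates in the first year. It is natural to expect baseline to track the 3-month value more closely than the 12-month value. A shared slope would then be too steep at 12 months, and chance baseline differences between arms would be over-corrected. That adds variance to the 2.5 mg/kg test and to each middle-dose test. Chance imbalance is largest in the smallest arms, so the middle-dose comparisons that identify the minimally effective dose are the most exposed.

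**Working it through.** **The plan's own figure.** Inputs from the sample size section: SD 0.27, difference 0.22, two-sided 5%, power 90%. n per arm = 2 × (0.27/0.22)² × (1.960 + 1.282)² = 31.7, so 32, as stated. The exact t calculation gives 89.4% power at 32 per arm. This is an unadjusted two-sample t-test; baseline plays no part in it.

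**Arm sizes.** Placebo and 2.5 mg/kg each receive 6 + 3 + 3 + 4 × 5 = 32. The middle doses share 114 − 64 = 50. A middle dose used only in cohort 1 has 6 participants, and one used in every cohort has 6 + 3 + 3 + 20 = 32. An even split over the three doses of cohort 1 gives about 17 each.

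**Formula.** With complete data and slopes treated as known, the variance of a 12-month contrast is

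(1/n₁ + 1/n₂) × [residual variance at 12 months + (b_c − b₁₂)² × Var(baseline)],

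where b₁₂ is the baseline slope at 12 months and b_c is the shared slope. The second term is never negative. A baseline-by-visit term removes it. The shared slope depends on the covariance:

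- Participant random intercept: b_c is the plain mean of the three visit slopes, so month 12 has weight one third and the two earlier visits two thirds.
- Unstructured: b_c is the mean weighted by the inverse residual covariance. When correlations decay, month 3 takes most of the weight.

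**Assumptions.** The protocol gives no correlations. I assume baseline correlations with months 3/6/12 as listed below; correlations among follow-up visits of 0.85 (3 with 6), 0.68 (3 with 12) and 0.78 (6 with 12); and equal SDs, so each slope equals its correlation.

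**Worked case, 0.80/0.70/0.55.** Residual variance at 12 months is 1 − 0.55² = 0.6975 (in units of 0.27²).

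- Random intercept: b_c = (0.80 + 0.70 + 0.55)/3 = 0.683. Added variance (0.683 − 0.55)² = 0.0178. Loss 0.0178/0.6975 = 2.5%.
- Unstructured: weights 0.72, 0.11 and 0.16 give b_c = 0.748. Added variance (0.748 − 0.55)² = 0.039. Loss 0.039/0.6975 = 5.6%.

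**All cases** (variance loss; then power for 32 v 32 at 0.22 on 60 df, one slope v visit-specific slopes):

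| Correlations | Random intercept | Unstructured |
|---|---|---|
| 0.65/0.65/0.65 | 0%; 98.8 v 98.8 | 0%; 98.8 v 98.8 |
| 0.75/0.70/0.60 | 1.1%; 97.9 v 98.0 | 1.6%; 97.8 v 98.0 |
| 0.80/0.70/0.55 | 2.5%; 96.7 v 97.0 | 5.6%; 96.2 v 97.0 |
| 0.85/0.75/0.60 | 2.8%; 97.7 v 98.0 | 6.4%; 97.3 v 98.0 |
| 0.85/0.70/0.45 | 5.9%; 93.7 v 94.9 | 22%; 90.2 v 94.9 |

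**Middle dose.** For 16 v 32, effect 0.20, 44 df, unstructured covariance: 0.79 v 0.81 at 0.80/0.70/0.55, and 0.67 v 0.75 at 0.85/0.70/0.45. Without any baseline adjustment, power is 0.66 (46 df).

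**Unequal SDs.** If the SDs at 3 and 6 months are 10% and 5% above the 12-month SD, the 0.80/0.70/0.55 losses become 4.2% (random intercept) and 7.9% (unstructured).

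**Simulation check.** I simulated the random-intercept estimator with 114 participants in five arms of 32/32/18/16/16, 20,000 trials per case. Losses were −0.3%, 0.7%, 2.4% and 5.9% for the first, second, third and fifth rows. The −0.3% is the price of the extra term when the slopes are equal. Both contrasts averaged zero under no effect, to within simulation error.

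**The case against.** The strongest reply is that the model is not settled. The primary-analysis section calls it a linear regression of the 12-month endpoint, and a regression on that visit alone would have no shared slope. The missing-data section restates the model without baseline, and the article defers detail to a statistical analysis plan. Part of this stands: the two sections need to be aligned. But time, time-by-dose and a participant random effect cannot be fitted to a single visit. The article also chose to interact dose with time and not baseline, so it is a stated list of terms rather than an omitted detail.

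The second reply is that the premise is assumed. That stands. The Background compares average first-year loss in children and adults; it gives no correlation and says nothing about 3 against 12 months.

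A reader might go further in three ways that the documents do not support:

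- **That early visits dominate whatever covariance is used.** Under the random intercept named in the primary-analysis section, the three visits count equally. Early visits dominate only under the unstructured form with decaying correlations, and that form is conditional on the data allowing it.
- **That the primary test is biased or its error rate inflated.** With complete data it is neither; a shared slope is a legitimate, less efficient adjustment.
- **That the planned power is lost.** The 90% does not rely on baseline adjustment. In every equal-SD case tabulated, the one-slope model has at least the unadjusted 89.4%. Only with steep decay, an unstructured covariance and the shrinking SDs above does it dip just below, to 88.6%.

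**Conclusion.** The point holds as a minor efficiency refinement. As written, the primary repeated-measures model adjusts the 12-month contrasts with a baseline slope shared by all three visits. If the relation to baseline weakens over the year, the avoidable variance is about 1-3% with a random intercept and about 2-6% with an unstructured covariance, for mild to moderate decay and equal SDs. Steep decay gives about 6% and 22%, and equal slopes give none. For 2.5 mg/kg at the planned effect this is less than one point of power in the mild and moderate cases. For a middle dose with 16 participants under moderate decay and an unstructured covariance it is about two points. All of these sizes rest on assumed correlations and complete data.

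**What to change.** Add baseline ln(AUC+1) by categorical visit to the primary model, and define each dose-versus-placebo comparison as the difference at the 12-month visit from that model. State the same model, including the baseline terms and one choice of covariance with its fallback, in the missing-data section, so that the two sections describe a single analysis.

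The cost is two extra parameters, or about 0.3% of variance if the slopes turn out equal. No new data are needed and trial conduct is unaffected. The article places the analysis plan before final database lock, so the term can still be specified there.
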